#### Further assessments

Besides the assessment of the outcome measures as listed above, several additional assessments will be conducted for screening reasons (Background medical history, Intake/prescription of concomitant medications, standard neurological examination, Florida Apraxia Screening Test - FAST
[28], Albert's Neglect Test - ANT
[29], Mini Mental Status Examination - MMSE
[30], Edinburgh Handedness Inventory - EHI
[31], Beck Depression Inventory - BDI
[32], Modified Medical Research Council Scale for measuring hand muscles - MRC-Index
[33]). The BDI
[32] will be conducted throughout all assessment time points due to the fact that depressive symptoms can evolve in all phases of the study and can therefore prevent an unhindered conduction of the training.

### Sample size

The calculation of the sample size is based on the aim to detect a difference of 2.5 points in the WMFT
[16] between the videotherapy- and the standard group concerning the change from baseline until the end of rehabilitation, corresponding to δ = 0.5, with a power of 90% in the final of two analyses. The critical difference of 2.5 points in the WMFT
[16] results from our pilot study
[10-13]. Allowing for a maximal drop out of 20% of the patients, 125 patients need to be included in the study for each group, rendering a total sample size of 375 (α_2_(1) = 0.035, Mann–Whitney test).

The interim analysis is conducted according to Wang and Tsiatis
[34], after half of the patients in each group (63 in each group, a total of 188) have concluded the rehabilitation program. If the effect is considerably greater than assumed (δ = 0.7, corresponding to a difference of 3.5 change points), there is a probability of 80% to detect this at this early stage and hence to terminate the study early.

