#### Primary endpoint

The score difference cannot be assumed to be normally distributed, so that distributions will be compared by analyzing the probability that an observed change score X_Videotherapy_ in the videotherapy population is greater than an observation in the non-video X_Non-video_ or the standard population X_Standard_:

H01:·PXVideotherapy>XStandard=12versusH11:·P(XVideotherapy>XStandard)≠12

and

H02:·PXVideotherapy>XNon−video=12versusH12:·P(XVideotherapy>XNon−video)≠12

The comparisons will be performed in a hierarchical manner according to a suggestion by Wiens
[36,37]. For this procedure, the total significance level α is split into one portion for the first hypothesis α(1) and one for the second hypothesis α(2) = α – α(1). Accordingly, as we expect a major difference between the novel video-based rehabilitation and the standard physiotherapeutic rehabilitation, this difference will be tested first at the significance level α(1). If the null hypothesis can be rejected, we will secondly test the difference between videotherapy and non-video at the full significance level α. However, if the first hypothesis cannot be rejected, the second hypothesis can still be tested at the significance level α(2). The hypotheses will be tested using the exact *U*-test according to Mann and Whitney, and the specific significance levels are fixed using a sequential analysis plan (see Table
3).

**Table 3 T3:** Procedure of statistical analysis

**Analysis i**	**Time point**	**Hypothesis**	**Nominal level α**_**i**_	**Detectable effect δ**_**i**_	**Power**
1	Interim analysis	Video vs. standard	0.01	0.7	80%
		Video vs. non-video	0.01	0.7	80%
2	Final analysis	Video vs. standard	0.035	0.5	90%
		Video vs. non-video	0.01 or 0.045	0.47 or 0.55	90%

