#### Interim analyses

After half of the patients have concluded the rehabilitation program, an interim analysis will be performed. This will allow for an early termination of the study if the effects are greater than assumed for sample size determination while keeping an overall significance level of α = 0.05. The interim analysis is planned according to the designs suggested by Wang and Tsiatis
[34] and yields a nominal significance level of α1 = 0.01 for the interim analysis. At this time point, all three null hypotheses regarding the primary endpoint as stated above are tested at the full nominal significance level, and the study is terminated only if all null hypotheses are rejected.

For the final analysis, the three hypotheses of the primary endpoint are tested at a nominal significance level of α2 = 0.045 in the hierarchical manner described above. Specifically, the first hypothesis is tested at a significance level of α2(1) = 0.035. If this null hypothesis is not rejected, the second null hypothesis is tested at the remaining significance level of α2(2) = 0.01. However, if the first null hypothesis is rejected, the second is tested at the full nominal significance level of α2 = 0.045.

This procedure renders the following effects detectable in the different stages, as presented in Table
3. The effects are measured by the differences of medians, for which 95% confidence intervals (Hodges-Lehmann) are computed for both group comparisons.

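### The 80% chance of stopping at the interim is the power of one comparison; under the plan's own rule that all nulls be rejected, the chance of stopping is about 66–69%

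*Protocol article*

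**What the plan says.** All passages are in the protocol article.

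- **Sample size.** The final analysis is sized at 125 enrolled per group, allowing for up to 20% drop-out, for an effect "corresponding to δ = 0.5, with a power of 90% in the final of two analyses". The interim takes place "after half of the patients in each group (63 in each group, a total of 188) have concluded the rehabilitation program". The larger effect is introduced with "If the effect is considerably greater than assumed (δ = 0.7, corresponding to a difference of 3.5 change points", and for it "there is a probability of 80% to detect this at this early stage and hence to terminate the study early".
- **Statistical analysis, Primary endpoint.** Two null hypotheses are defined: videotherapy versus standard and videotherapy versus non-video. Both are two-sided. Table 3 gives 80% power at effect 0.7 and level 0.01 on a separate line for each.
- **Interim analyses.** The design "yields a nominal significance level of α1 = 0.01 for the interim analysis". The section counts three primary null hypotheses, tests each at that level, and states that "the study is terminated only if all null hypotheses are rejected".
- **Secondary endpoints.** Non-video versus standard appears here, as an exploratory test at 0.05.

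**The concern.** The Sample size section treats detecting one effect as the same event as stopping the trial. Under the stopping rule it is not: the trial stops only when every primary null is rejected. The 80% in Table 3 is the power of a single comparison, so it cannot also be the probability of stopping at the same sample size.

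Two ambiguities make the true figure hard to recover. The text does not say whether patients who have concluded the programme include drop-outs whose treatment period has passed. The Interim analyses section also counts three nulls where the Primary endpoint section defines two.

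At stake is a stated design property, the chance that a large effect ends the trial early, together with a clear trigger for the interim analysis.

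**Working it through.** **Inputs.** 125 enrolled per group, 20% drop-out, 63 per group at the interim, effect 0.7, 80% (Sample size); two-sided hypotheses (Primary endpoint); levels 0.01 at the interim and 0.035 within 0.045 at the final (Interim analyses). Assumptions of this check: normal shift with SD 1, and Mann–Whitney efficiency 3/π relative to the t-test.

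**1. Evaluable numbers.** Final: 125 × 0.8 = 100. Interim, with the same allowance: 63 × 0.8 = 50.4.

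**2. Reproducing the final power.** Power = Φ(δ·√(n/2 · 3/π) − z). With δ = 0.5, n = 100 and z = 2.108 (two-sided 0.035): Φ(3.455 − 2.108) = 0.91. Noether's formula gives 0.90. The stated 90% is reproduced on 100 evaluable.

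**3. Power per comparison at the interim**, δ = 0.7, z = 2.576:

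- n = 50: Φ(3.420 − 2.576) = Φ(0.844) = 0.80.
- n = 63: Φ(3.839 − 2.576) = Φ(1.263) = 0.90.

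| Method | 50 per group | 63 per group |
|---|---|---|
| Efficiency-adjusted normal | 0.801 | 0.897 |
| Noncentral t | 0.806 | 0.903 |
| Unadjusted normal | 0.822 | 0.912 |
| Noether | 0.761 | 0.867 |
| Simulation, 10,000 runs | 0.773 | 0.890 |

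Table 3's 80% belongs to about 50 evaluable per group (48 to 54, depending on the formula). With 63 evaluable, the effect detectable with 80% power would be 0.62, not 0.7.

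**4. Probability of rejecting both defined nulls.** The two comparisons share the videotherapy arm. With equal arms their statistics correlate at about 0.5. With effect 0.7 on both, the probability is the bivariate normal Φ₂(a, a; 0.5), with a taken from step 3:

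- n = 50: Φ₂(0.844, 0.844) = 0.69; simulation 0.66.
- n = 63: Φ₂(1.263, 1.263) = 0.83; simulation 0.81.

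**5. The two 80% statements side by side.**

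| Reading of the 63 | Per comparison (Table 3: 80%) | Stopping (Sample size: 80%) |
|---|---|---|
| Enrolled and past treatment, about 50 evaluable | about 80% | 66–69% |
| Evaluable completers | 87–91% | 81–83% |

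This does not depend on the formula. The probability of rejecting both cannot exceed that of rejecting either one, and it equals it only if one rejection always implies the other.

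**6. If a third null must be rejected.** In this shift model, effect 0.7 on both comparisons means that non-video and standard have the same distribution, so their null is true. It is rejected at level 0.01 at most about 1% of the time, and all three together less often: 0.3% in simulation at either sample size.

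**7. Type I error.** For two looks at 0.01 and 0.045, the overall two-sided level is 0.0498 at information 0.50 and 0.0483 at 0.63.

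**The case against.** The best defence is that the interim figures are coherent on the plan's own basis. Both 63 and 188 are rounded halves of enrolment (125/2 = 62.5 and 375/2 = 187.5). Taking off the planned 20% gives about 50 evaluable, exactly where 80% at effect 0.7 is reproduced. The primary analysis is by intention to treat with imputation, which fits a count that includes drop-outs. All of this stands, and on this reading Table 3 is correct.

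It also disposes of stronger readings:

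- A reader might set 63 completers against 100 evaluable and infer that the interim falls at 63% information and upsets the significance levels. The documents do not support this. On a consistent basis the fraction is 50/100 = 0.50 or 63/125 = 0.504, and even at 0.63 the overall level is slightly conservative.
- A reader might see an error in 188 against 3 × 63 = 189. It is rounding.
- A reader might infer that the data and safety monitoring board is handed the 80% and decides on it. The text does not say so.

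The defence does not rescue the stopping probability. The reading that makes Table 3 right is the one on which 80% is furthest from the chance of stopping. It can fairly be said that 63 evaluable completers bring stopping close to 80%, but then Table 3 is too low.

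**Conclusion.** The point holds, limited to the stated probability of early termination. At about 50 evaluable per group it is overstated by 11 to 14 percentage points (80% against 66–69%). At 63 evaluable it is about right, but Table 3 then understates power per comparison by 7 to 11 points. If the third null is required and true, the chance of stopping is below 1%.

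The figures assume a normal shift, equal arms and effect 0.7 on both comparisons. The Primary endpoint section expects the major difference to be against standard; if the effect against non-video is below 0.7, stopping is less likely still.

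Type I error, sample size and final power are unaffected. This is a misstated design property and a loosely worded trigger, not a failure of the sequential design.

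**What to change.** 1. In Sample size and Interim analyses, state whether the 63 per group counts all randomised patients who have reached the end of treatment (about 50 evaluable) or evaluable completers.
2. In Interim analyses, change three hypotheses to the two of the Primary endpoint section, or state that non-video versus standard must also be rejected and give the resulting stopping probability.
3. In Sample size, report power per comparison separately from the probability of stopping, with the assumed effects. With two hypotheses and effect 0.7 on both, this is 80% and about 66–69% at 50 evaluable, or about 90% and 81–83% at 63. In the second case, correct Table 3's interim rows as well.

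The levels 0.01 and 0.045 may stay. The cost is rewording two paragraphs and, if completers are meant, two table rows. No extra patients are needed.

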### Randomization: sequence generation

According to Nordle and Brantmark
[35], a self-adjusting randomization plan with an allocation probability of 0.9 is utilized with stratification for center as the more important and the MRC-Index (reached scores 2, 3, and 4)
[33] as the less important factor.

### Randomization: implementation

The allocation of patients will be conducted by an investigator without any clinical involvement in the trial using proper random sequences unbeknown to the patients or study team: The randomization and further allocation is performed centrally via fax at the Institute of Medical Biometry and Statistics at the University Hospital Schleswig-Holstein, Campus Lübeck, Germany (IMBS) after the respective investigator had screened the respective patient and obtained his/her written informed consent.

### Blinding

Participants are to be enrolled by the respective trial sites' personal.

Participating patients can only be blinded for the comparison of the videotherapy versus the non-video condition, but not for the comparison with the standard rehabilitation. Hence, comparing videotherapy with standard might be biased by the knowledge of the patients to receive a novel treatment. In addition, the intensity of rehabilitation will be comparable between the videotherapy and the non-video group, but not necessarily between both motor exercise groups and the standard group. Therefore, a difference between videotherapy and standard might be caused by a more intense training in the first group. These possible influences will have to be considered in the interpretation of possible study outcomes.

### Statistical analysis

#### Study population

According to the "ICH Topic E 9" there are two different sets (intention to treat set and per protocol set) for the statistical analysis.

The primary analysis will be based on the intention to treat population where missing values will be imputed with a mean imputation. Similar rates of missing baseline observations between the treatment groups as well as analogous results from sensitivity analyses will be used to support the interpretation. As sensitivity analyses, the imputation methods "Last Observation Carried Forward" principle and best or worst case imputation will be applied.

A secondary analysis will be based on the per protocol population. Here we consider only patients which complete at least 66,67% of the training sessions. This value is derived from the pilot study
[10], where significant treatment effects occurred after duration of 20 training days. The analyses will be the same as with the intention to treat.

#### Primary endpoint

The score difference cannot be assumed to be normally distributed, so that distributions will be compared by analyzing the probability that an observed change score X_Videotherapy_ in the videotherapy population is greater than an observation in the non-video X_Non-video_ or the standard population X_Standard_:

H01:·PXVideotherapy>XStandard=12versusH11:·P(XVideotherapy>XStandard)≠12

and

H02:·PXVideotherapy>XNon−video=12versusH12:·P(XVideotherapy>XNon−video)≠12

The comparisons will be performed in a hierarchical manner according to a suggestion by Wiens
[36,37]. For this procedure, the total significance level α is split into one portion for the first hypothesis α(1) and one for the second hypothesis α(2) = α – α(1). Accordingly, as we expect a major difference between the novel video-based rehabilitation and the standard physiotherapeutic rehabilitation, this difference will be tested first at the significance level α(1). If the null hypothesis can be rejected, we will secondly test the difference between videotherapy and non-video at the full significance level α. However, if the first hypothesis cannot be rejected, the second hypothesis can still be tested at the significance level α(2). The hypotheses will be tested using the exact *U*-test according to Mann and Whitney, and the specific significance levels are fixed using a sequential analysis plan (see Table
3).

**Table 3 T3:** Procedure of statistical analysis

**Analysis i**	**Time point**	**Hypothesis**	**Nominal level α**_**i**_	**Detectable effect δ**_**i**_	**Power**
1	Interim analysis	Video vs. standard	0.01	0.7	80%
		Video vs. non-video	0.01	0.7	80%
2	Final analysis	Video vs. standard	0.035	0.5	90%
		Video vs. non-video	0.01 or 0.045	0.47 or 0.55	90%

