## Methods/design

### Trial design

The form of our clinical study will be: multicenter, open, randomized, placebo-controlled, paralleled group trial with three investigative arms conducted in Germany (5 sites). This study aims at demonstrating superiority of the videotherapy over both physical training and standardized physical therapeutic treatments. We will use equal number of patients for the randomization on the three groups (1:1:1).

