The multicenter study will take place at 5 sites in Germany: Department of Neurology of University of Leipzig, Department of Neurology of Brandenburg Klinik Bernau near Berlin, Clinic for Neurology of at Campus Lübeck University Medical Center Schleswig-Holstein, St. Mauritius Therapieklinik at Meerbusch near Düsseldorf, and the Neurological Centre of Segeberger Kliniken GmbH at Bad Segeberg. All sites represent the main venues for stroke patients and stroke-related rehabilitation in their surrounding areas, thus able to reach the expected sample size of stroke patients. Because the study centers at Lübeck and Leipzig do not provide treatment for patients in their post-stroke rehabilitation phase, these sites will recruit patients from nearby rehabilitation centers to where their sub-acute patients have been referred further on. Recruited patients therefore will have been pre-screened at the respective site and will be invited at the end of their rehabilitative treatment to the trial site for participation. All recruitment formalities and ambulatory or stationary assessments will be conducted in the sites stated above with patients transported to the respective clinics.

Patients' data will be assessed in the respective sites. Data management and monitoring of the trial sites will be conducted by the Center for Clinical Trials, University of Lübeck. Biostatistical analysis and randomization will be performed by the Institute of Medical Biometry and Statistics, University of Lübeck. An independent Data and Safety Monitoring Board (DSMB) of two clinicians and a biostatistician will to supervise patients' safety, as well as statistical analysis and interpretation.

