#### Primary endpoint

The primary efficacy endpoint is the change in scores of the WMFT
[16] between baseline and after six weeks of rehabilitation treatment between the videotherapy group, the standard and videotherapy group and the non-video group.

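### The primary Mann–Whitney test omits centre and MRC grade, the factors used to balance allocation; it stays valid, but if they predict WMFT change it is conservative and gives up a little power

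*Protocol article*

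**What the plan says.** - **Allocation.** The section on sequence generation states that "a self-adjusting randomization plan with an allocation probability of 0.9 is utilized with stratification for center as the more important and the MRC-Index" grade (2, 3 or 4) as the less important factor. There are five centres, and allocation to the three groups is 1:1:1.
- **Endpoint.** In the Outcomes section, "The primary efficacy endpoint is the change in scores of the WMFT" from baseline to the end of six weeks of treatment.
- **Test.** Under Statistical analysis, Primary endpoint: "The hypotheses will be tested using the exact *U*-test according to Mann and Whitney". No strata or covariates are named. The hypotheses are two-sided and concern the probability that a videotherapy change score exceeds a control change score.
- **Levels.** Under Interim analyses, "the first hypothesis is tested at a significance level of α2(1) = 0.035" at the final analysis. The second hypothesis is then tested at 0.045 or at 0.01, depending on the first result. The interim level is 0.01.
- **Sample size.** It is computed for the Mann–Whitney test: δ = 0.5, level 0.035, power 90%, 20% dropout, 125 per group.
- **Other uses of these variables.** Centre returns as one of the subgroup variables. MRC grade appears in no analysis.

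**The concern.** The exact U-test takes its null distribution from all group labellings of the given sizes, treated as equally likely. An allocation plan that favours the balancing arm with probability 0.9 makes labellings that are unbalanced on centre or MRC grade rare. If those factors predict WMFT change, the U-statistic varies less across the allocations that can really occur than the test assumes. The test then rejects less often than its nominal level under the null, and it is less powerful than a test that uses the factors.

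Choosing the two factors for balancing suggests that the sponsor thought them prognostic, and they are recorded for every patient. Baseline WMFT is a separate matter. It is not a balancing factor, so leaving it out as a covariate only forgoes precision. What is at stake is efficiency in the two confirmatory comparisons, not their validity.

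**Working it through.** **Inputs from the article:** two-sided level 0.035 (critical value 2.108), δ = 0.5, power 90% (1.282), 20% dropout, 125 randomised and so 100 evaluable per group, five centres, three MRC grades, allocation probability 0.9. **Assumed:** R², the share of within-group variance in WMFT change explained by the factors, which the article does not give. The range used is 0 to 0.20.

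**1. The plan's own figure (Noether's formula).** p = Φ(0.5/√2) = 0.638. Then n = (2.108 + 1.282)² / [6 × (p − 0.5)²] = 100.3 per group, and 100.3/0.80 = 125.4, against 125 stated. Power at 100 per group is Φ(√600 × (p − 0.5) − 2.108) = Φ(3.384 − 2.108) = 89.9%. The stated sample size reproduces.

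**2. True size of the unadjusted test.** If balance is close to complete, the part of the variance due to the factors drops out of the group difference. The standardised U then has standard deviation of about √(1 − R²) instead of 1, so size = 2 × [1 − Φ(2.108/√(1 − R²))].

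**3. Power of each test.** Unadjusted: Φ((3.384 − 2.108)/√(1 − R²)). Adjusted: step 1 with δ replaced by 0.5/√(1 − R²), which gives Φ(3.559 − 2.108) at R² = 0.10 and Φ(3.765 − 2.108) at 0.20.

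| R² | True size, U-test | Power, U-test | Power, adjusted | Difference (points) |
|---|---|---|---|---|
| 0 | 0.035 | 89.9% | 89.9% | 0 |
| 0.10 | 0.026 | 91.1% | 92.7% | 1.6 |
| 0.20 | 0.018 | 92.3% | 95.1% | 2.8 |

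**4. Simulation check.** 3,000 trials per scenario, three-arm minimisation at probability 0.9 with centre weighted double, R² split equally between the two factors, normal outcomes, about 100 per arm. The U-test used its normal approximation. Rank ANCOVA had centre and MRC grade as main effects.

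| R² | Size, U-test | Size, rank ANCOVA | Power, U-test | Power, rank ANCOVA |
|---|---|---|---|---|
| 0 | 0.035 | 0.036 | 91.1% | 91.2% |
| 0.10 | 0.024 | 0.032 | 91.6% | 93.1% |
| 0.20 | 0.018 | 0.036 | 92.4% | 95.3% |

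The Monte Carlo standard error of a size is about √(0.035 × 0.965/3,000) = 0.003, so the two approaches agree. At R² = 0.30 the size of rank ANCOVA was 0.041, less than two standard errors above nominal. A van Elteren test over the 5 × 3 = 15 centre-by-grade cells had power 87.1% at R² = 0, below the U-test. With 200/15 ≈ 13 patients per cell across two arms, the cells are sparse.

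**5. Baseline WMFT.** If baseline and six-week scores have equal variance and correlation ρ (not given), baseline explains (1 − ρ)/2 of the variance of the change: 5% at ρ = 0.9, 10% at 0.8, 20% at 0.6. Baseline is not balanced by design, so the U-test's own power does not rise with this share. Adjusting for baseline alone would take power from 89.9% to 91.3%, 92.7% and 95.1% respectively. The share may overlap with that of MRC grade, so the gains should not be added.

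**6. The 0.01 level.** With 2.576 in place of 2.108 and δ = 0.5 at 100 per group, the unadjusted and adjusted powers are Φ(0.808/√0.9) = 80% and Φ(0.983) = 84% at R² = 0.10, and Φ(0.808/√0.8) = 82% and Φ(1.189) = 88% at R² = 0.20. At the final analysis this applies to videotherapy versus non-video only if the first hypothesis is not rejected.

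**The case against.** The strongest reply is that nothing promised is missed. The trial is sized for the unadjusted test, that size reproduces, and type I error stays at or below nominal. The loss depends wholly on an R² that the article does not give. Eligibility is already limited to MRC 2 to 4, which may limit what MRC grade can explain. The U-test is prespecified, needs no normality and matches the stated hypotheses. All of this stands, and it limits the point to an efficiency gain.

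Three stronger readings are tempting, and the document supports none of them:

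- A reader might infer that the test ignores baseline WMFT and is conservative for that reason. Baseline is used by subtraction, and because it is not a balancing factor its omission as a covariate cannot make the test conservative.
- A reader might compare the adjusted power of 92.7% or 95.1% with 89.9% and report a loss of about 3 to 5 points for centre and MRC grade. That overlooks that balance also raises the U-test's own power, to 91.1% or 92.3%.
- A reader might state as fact that the true type I error is below nominal. At R² = 0 it is not.

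The objection that a fully stratified test would be a poor replacement also stands: van Elteren over 15 sparse cells can lose power and cannot adjust for baseline. It does not count against a main-effects rank analysis, which lost nothing at R² = 0 in the simulation.

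**Conclusion.** The point holds as a modest, low-cost improvement to a stated analysis rule. The planned test is valid and has its planned 90% power. If centre and MRC grade together explain 10% to 20% of the variance of WMFT change, its true size at nominal 0.035 is about 0.026 to 0.018, and about 1.5 to 3 points of power are given up against an adjusted test. If they explain nothing, nothing is lost. Adjusting for baseline WMFT could add further efficiency, depending on an unstated correlation. These figures rest on the assumed R², near-complete balance, 100 evaluable patients per group and approximately normal change scores. There is no bias and no shortfall against the plan.

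**What to change.** Make the primary test for both confirmatory comparisons a rank-based analysis adjusted for centre, MRC grade and baseline WMFT, at the same nominal levels, at interim and final analysis. Rank ANCOVA would serve. So would a covariate-adjusted probabilistic index, which stays on the scale of the stated hypotheses. Enter centre and MRC grade as main effects rather than as 15 strata. Keep the exact U-test with the Hodges–Lehmann interval as a sensitivity analysis, and note that the sample size was computed for the unadjusted test. Fix the model before the interim analysis.

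One check goes with this. Table 2 places the baseline WMFT in week 2, after the week 1 instruction of the two training groups. The covariate should be a value unaffected by allocation; the planned change score has the same dependence.

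The cost is wording and a little programming, with no new data or patients. The test is no longer exact, and the adjusted effect is conditional rather than marginal, which the text should say.
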